#### PRP preparation

Platelet-rich plasma will be prepared using a commercially-available product (Regen Lab SA), which yields a platelet concentration factor of 1.6 to 5 times over whole blood values, and with approximately 80% platelet recovery [23]. After the blood draw into the Regen blood collection tubes, the tube will be gently inverted several times to mix the anti-coagulant with the blood sample. Samples will then be centrifuged at 1500 g for 5 min in a separate room by the study nurse. After centrifugation, the tubes will be gently agitated to ensure all visible platelet aggregates detach from the separating gel and the tube wall, and 5 mL will be gently withdrawn into a syringe. At the Melbourne site only, a portion of the PRP (approximately 4 mL) will be withdrawn and saved for analysis. A video of the PRP preparation procedure can be found in at https://www.youtube.com/watch?v=Cq8UlbL18Yg&feature=youtu.be.

#### Saline injections

The placebo group will have the blood sample taken as per the PRP group to assist blinding. The research nurse will discard the sample in a separate room, and then prepare a syringe with a saline solution (5 mL), attach a needle and place a patient label over the syringe and needle base to occlude the contents. The nurse will then deliver the syringe to the treating doctor for injection.

### Outcome measures

Study outcome measures are presented in Table 1. Our two primary outcome measures are 12-month change in overall average knee pain severity and medial tibial cartilage volume:i)*Average overall knee pain severity*: this will be measured at baseline, 2, 6, 9 and 12 months using an 11-point numeric rating scale (NRS) with terminal descriptors ‘no pain’ (score 0) and ‘worst pain possible’ (score 10). This was chosen because it has well-established clinimetric properties in knee OA and established minimal clinically important differences [24], and is a recommended measure for knee OA RCTs from the Osteoarthritis Research Society International [25].ii)*Medial tibial cartilage volume*: an MRI scan of the study knee will be performed at baseline and 12 months using a 3 T whole body system with a dedicated extremity coil and a T1-weighted fat-suppressed 3D gradient recall acquisition sequence (Additional file 1). Medial tibial cartilage volume will be measured by manually drawing disarticulation contours around the cartilage edges, section by section. To reduce measurement error and bias, one person will measure each participant’s paired set of images, blinded to time sequence and treatment allocation. Regular quality review will occur in 20% of images by a second reader. Our coefficients of variation for these measures are 2.3–2.4% [26].

The following secondary outcome measures will also be collected:i)*Average knee pain severity during walking*: measured at baseline, 2 months and 12 months on an 11-point NRS, where 0 indicates no pain and 10 indicates worst pain possible.ii)*Intermittent and Constant Osteoarthritis Pain (ICOAP) questionnaire:* measured at baseline, 2 months and 12 months. This is a self-report multi-dimensional, OA-specific measure of pain experience, with established reliability, internal consistency and validity in people with knee OA [27]. It is comprised of 5-items assessing constant knee pain in the previous week, and 6-items assessing intermittent knee pain in the previous week. Questions regarding pain intensity have terminal responses of ‘not at all’ (score 0) and ‘extremely’ (score 4), and questions regarding pain frequency have ‘never’ (score 0) to ‘very often’ (score 4). Total scores range from 0 to 100, with higher scores indicating worse pain.iii)*Knee Injury and Osteoarthritis Outcome Score:* measured at baseline, 2 months and 12 months. This is a knee-specific self-report outcome measure with high test-retest reliability, internally consistent and face and content validity [28, 29]. Likert responses range from None to Extreme, and scores range from 0 to 100, with lower scores indicating worse symptoms, function or quality of life. It is comprised of the following five subscales:Pain: scored from 9 questions about knee pain frequency experienced in the last week, and the amount of knee pain experienced during specific activities such as twisting, bending and walking.Other symptoms: scored from 7 questions regarding other symptoms experienced in the last week, such as swelling, restricted range of motion and mechanical symptoms.Function in daily living: scored from 17 questions regarding knee function in the last week.Function in sport and recreation: scored from 5 questions regarding function with sport and recreational activities in the last week.Knee-related quality of life: scored from 4 questions about knee-related quality of life experienced in the last week.iv)*Participant-perceived global ratings of change:* participants will rate perceived overall change with treatment (compared to baseline), and change in pain and physical function, on a 7-point Likert scale (from “much worse” to “much better”) at 2 and 12 months [30]. Those ‘moderately better’ or ‘much better’ will be classified as improved. All other respondents will be classified as not improved.v)*Health-related quality of life:* measured at baseline, 2 months and 12 months using the 35-item Assessment of Quality of Life (AQoL-8D) instrument [31]. The AQoL-8D has strong psychometric properties and is more responsive than other widely-used scales [32]. Scores range from − 0.04 to 1.00, with higher scores indicating better quality of life. The AQoL-8D will also be measured at 6 and 9 months for the health economic evaluation.vi)*Other MRI-derived measurements*: using a 3 T whole body system with a dedicated extremity coil and a T1-weighted fat-suppressed 3D gradient recall acquisition sequence (Additional file 1). Outcomes include:MRI osteoarthritis knee score (MOAKS): an OA-specific semi-quantitative tool evaluating multi-feature joint changes associated with OA [33]. We will assess the following subscores: meniscal morphology (any regions with worsening at 12 months compared to baseline; scored as yes or no); inter-condylar synovitis (worsening in inter-condylar synovitis at 12 months compared to baseline; scored as yes or no); cartilage morphology (number of areas with worsening in thickness at 12 months compared to baseline; categorised as 0, 1, 2, or 3+); and whole knee effusion (change in whole knee effusion at 12 months compared to baseline; categorised as worsened, no change or improved).Bone marrow lesion size: assessed from the MRIs at baseline and 12-months using categorical scoring in the medial distal femur and the proximal tibia (range 0–3 per region, with higher scores indicating greater bone marrow lesion size). Progression of bone marrow lesions (yes/no) will be defined as an increase in score by at least 1 from baseline to follow-up in either the medial tibial or medial femoral compartment.Cartilage defects: score in the medial distal femur and the proximal tibia at baseline and 12-months using categorical scoring (range 0–4 per region, with higher scores indicating greater cartilage defects). Progression of medial cartilage defects (yes/no) will be defined as an increase in score by at least 1 from baseline to follow-up in either the medial tibial or medial femoral compartment.

We will also collect a number of additional measures, as well as data regarding participant descriptive characteristics, health services usage and cytokine and growth factor profiles:i)*Additional measures*: these include participant weight, drug/supplement use, adverse events, the success of participant and doctor blinding, use of co-interventions and number of injections.ii)*Descriptive data*: including participant height, body mass index, age, gender, duration of symptoms, radiographic disease severity, knee alignment (measured from the knee x-ray and reported in degrees [34]), current employment, symptom laterality, symptoms in other joints, treatment expectation on a 5 point Likert scale (from “no effect at all” to “complete recovery”), neuropathic pain using the painDETECT questionnaire [35], and physical activity using the Physical Activity Scale for the Elderly (PASE) [36, 37]. The cross-sectional area of the medial tibial plateau from MRI [30] will be measured for use as a covariate.iii)*Health economic evaluation data*: measured using data collected at baseline, and 2, 6, 9 and 12-months. Data include health care costs estimated from healthcare service usage and Quality Adjusted Life Years (QALYs) calculated using the AQoL-8D, and work performance data obtained from the World Health Organisation Health Performance Questionnaire (WHO HPQ) [38].iv)*Cytokine and growth factor concentrations:* aliquots of PRP will be analysed in a subset of participants to determine the concentration of key growth factors and cytokines, such as platelet-derived growth factor, transforming growth factor beta 1, connective tissue growth factor, interleukin 1 receptor agonist, interleukin 1 beta, interleukin 6 and matrix metallopeptidase 9.

### Participant compliance

Compliance will be reported as the number of injections administered. Compliance with the injection schedule will be monitored by the site coordinators and the staff at the radiology clinics, who will be responsible for booking participants in for injection procedures.

### Adverse effects of treatment and co-interventions

Adverse events are defined as any untoward medical occurrence in a trial participant which does not necessarily have a causal relationship with the treatment. Adverse events will be collected via self-report during the 2- and 12-month data collection, and by the study nurse following each injection. This will include questions about any adverse events that participants believe may be related to the study intervention, including their nature, how long they lasted for and what action if any, they took (e.g. taking medication or seeing a health professional). Serious adverse events are defined as any untoward and unexpected medical occurrence that results in death, is life-threatening, requires hospitalisation or prolongation of existing inpatient’s hospitalisation, results in persistent or significant disability or incapacity, is a congenital anomaly or birth defect, or any other important medical condition which may require medical or surgical intervention to prevent one of the outcomes listed [39]. Use of co-interventions (medications for knee pain and any other treatments for knee OA) will be recorded at 2 and 12-months.

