**Fig. 1 Fig1:**
[figure not shown]
Flow diagram of the study protocol

**Table 1 Tab1:** SPIRIT (Standard Protocol Items: Recommendations for Interventional Trials) diagram of enrolment, interventions and assessments for the RESTORE trial

Timepoint			Study period						
	Enrolment	Baseline	Injection 1	Injection 2	Injection 3	Post-allocation			Close-out
	-t_1_		0	1w	2w	2 m	6 m	9 m	12 m
Enrolment:									
Eligibility screen	X								
Informed consent	X								
Allocation		X							
Interventions:									
Platelet rich plasma			X	X	X				
Saline			X	X	X				
Assessments:									
Primary outcomes									
Average overall knee pain severity		X				X	X	X	X
Medial tibial cartilage volume		X							X
Secondary outcomes									
Walking pain severity		X				X			X
KOOS		X							
ICOAP		X							
Participant global ratings of change						X			X
AQoL-8D		X				X	X	X	X
MOAKS sub-scores		X							X
BML and cartilage defects score		X							X
Other measures									
Drug/supplement use		X				X			X
Cytokines and growth factors			X	X	X				
Number of injections			X	X	X				
Adverse events, co-interventions						X			X
Success of blinding					X				
Descriptive measures									
Weight, height, BMI		X							X
Age, gender, symptom duration, x-ray severity, knee alignment, employment, symptom laterality, other symptoms, treatment expectation, PainDETECT, PASE, knee effusion		X							
Health economic data									
QALYs, cost-effectiveness ratio, WHOHPQ		X				X	X	X	X

*ICOAP* Intermittent and Constant Osteoarthritis Pain, *KOOS* Knee Injury and Osteoarthritis Outcome Score, *AQOL-8D* Assessment of Quality of Life Instrument (8D version), *MOAKS* Magnetic resonance imaging OA Knee Score, *BMI* Body mass index, *PASE* Physical Activity Scale for the Elderly, *QALYs* Quality Adjusted Life Years, *WHO HPQ* World Health Organisation Health Performance Questionnaire

Paper-based or electronic clinical and health outcome questionnaires will be sent to participants at 2, 6, 9 and 12 months to complete primary and secondary outcomes at home. Structural outcome measures recorded using MRI of the knee joint will be conducted at baseline and 12 months at radiology practices in Melbourne and Sydney. Ethical approval has been obtained from the University of Melbourne Human Research Ethics Committee (HREC No. 1647671) and the Northern Sydney Local Health Districts Human Research Ethics Committee (HREC/16/HAWKE/430). All participants will provide written informed consent.

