#### Blinding arrangements

Participants will not be told until the end of the study which group they were allocated to. Blood will be withdrawn from the arm of participants in both groups to ensure participant blinding. Blood from participants in the placebo group will be disposed of by the study nurse in a separate location. A study nurse will prepare the injection in a separate room and place a patient label over the syringe and needle base to occlude the contents. The nurse will then give the syringe to the injecting doctor who will not know or be able to tell whether the syringe has PRP or saline. The same preparation process will be in place for injection appointment 2 and 3. All clinical and MRI assessments will be conducted by an assessor blinded to treatment allocation.

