#### Interventions

Participants in both the PRP and placebo groups will undergo three intra-articular knee injections performed at weekly intervals, in line with commonly used injection protocols for this condition [16, 22]. The doctor will give the participant the option of having a local anaesthetic injection superficially (subcutaneously) before treatment. The doctor will then check the study knee for the presence of an effusion using ultrasound. If present and deemed to be amenable to aspiration, then this will be performed using a needle inserted in the suprapatellar bursa, and the volume aspirated will be recorded. The study nurse will give the doctor an occluded syringe with a needle containing 5 ml of either normal saline or PRP, and the contents will be injected into the knee joint under ultrasound guidance using a medial patellofemoral approach. Following the injection, passive knee flexion and extension will be performed five times with the participant observed resting for 10 min thereafter.

Participants will return for their second injection approximately 1 week later, and again for a third and final injection approximately 1 week after that. The injection process will be the same as the first injection. After the third injection, participants will be asked about which group they believe they are in, and separately the injecting doctors will also be asked which group they believe the participant is in. After each injection, the study nurse will ask the participant if they experienced any adverse events following the previous injection.

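### The serious adverse event definition requires the event to be unexpected, and the only self-report question content described is attribution-based; neither fits the protocol's own broad adverse event definition

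*Protocol article*

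**What the plan says.** The protocol article, under Adverse effects of treatment and co-interventions, begins broadly: "Adverse events are defined as any untoward medical occurrence in a trial participant which does not necessarily have a causal relationship with the treatment". That sentence sets no condition on cause or expectedness.

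The same paragraph then defines the serious subset: "Serious adverse events are defined as any untoward and unexpected medical occurrence that results in death", and goes on to list further criteria, hospitalisation among them.

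On collection it says: "Adverse events will be collected via self-report during the 2- and 12-month data collection, and by the study nurse following each injection". It describes the content as follows: "This will include questions about any adverse events that participants believe may be related to the study intervention", with details of nature, duration and action taken. Under Interventions, the nurse's enquiry is wider: "the study nurse will ask the participant if they experienced any adverse events following the previous injection".

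Table 1 agrees with the text and places adverse events and co-interventions at 2 and 12 months. The Procedures section also says: "Paper-based or electronic clinical and health outcome questionnaires will be sent to participants at 2, 6, 9 and 12 months". Under Outcome measures, adverse events are listed among the additional measures, not as a primary or secondary outcome.

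**The concern.** Seriousness concerns the outcome of an event. Expectedness concerns whether it was foreseen. The definition makes the second a condition of the first, so the serious count would leave out the foreseeable serious complications of the injection procedure. Readers of a safety table want to see those, because they bear directly on the decision to inject.

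The self-report raises a related problem. If an adverse event counts regardless of cause, a question that starts from the participant's own belief about cause is a poor instrument for finding it. A participant who does not connect an event with an injection given months before has no described prompt to report it.

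**Working it through.** The main check is textual. The article states no safety event rate or safety power, so there is no figure of its own to reproduce on this point.

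**Step 1: the two definitions side by side.**

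| | Untoward | Causal link required | Must be unexpected | Seriousness criterion |
|---|---|---|---|---|
| Adverse event | yes | no | no | no |
| Serious adverse event | yes | none stated | yes | yes |

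The serious subset should differ from the whole only in the last column. It also differs in the third.

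**Step 2: apply them to an example.** Take a hospitalisation for a complication that was foreseeable after a joint injection. It is untoward, so it is an adverse event. It meets the hospitalisation criterion. It is expected, so it fails the serious definition as worded. The result is an event that is recorded but not classed as serious.

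**Step 3: enquiries over follow-up.** Table 1 puts the injections at weeks 0, 1 and 2. The nurse's enquiry, which has no attribution condition, is tied to those visits. After them, the article describes only the self-reports at 2 and 12 months. Treating baseline and the first injection as the same day, about 52 − 2 = 50 of 52 weeks rest on the self-report. The interval between the two self-reports is 12 − 2 = 10 months. The article does not state the recall period of the 12-month item.

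**Step 4: what under-recording would do (illustration on assumed rates).** Take 144 per arm from the sample size section. Assume true risks p0 = 5% and p1 = 10%, and a captured share c that is the same in both arms. Then events = 144 × p × c, risk difference = (p1 − p0) × c, and risk ratio = (p1 × c)/(p0 × c).

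| c | Events, lower-risk arm | Events, higher-risk arm | Risk difference | Risk ratio |
|---|---|---|---|---|
| 100% | 144 × 0.05 = 7.2 | 144 × 0.10 = 14.4 | 5.0 points | 2.0 |
| 75% | 5.4 | 10.8 | 3.75 points | 2.0 |
| 50% | 3.6 | 7.2 | 2.5 points | 2.0 |

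With equal true risks of 5%, both arms fall together (7.2, 5.4 and 3.6 events) and the ratio stays at 1.0. Equal under-capture lowers the counts and the absolute difference but does not by itself favour an arm. The equal share is itself an assumption, which the article neither establishes nor excludes.

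**The case against.** The strongest reply has four parts.

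- **The questions are not stated to be restricted.** The article says collection will include questions on attributed events; it does not say only those. The nurse asks about any adverse event. A condensed article does not reproduce its forms. This stands. The fair criticism is limited to the content that is described, and to the period after the injection visits.
- **Nothing is lost by the serious definition.** An expected hospitalisation remains an adverse event, with its nature and the action taken recorded. This also stands: the fault is misclassification. A reader might infer that expected serious events vanish from the record, and the text does not support that.
- **No bias between arms is shown.** A reader might infer that counts would be distorted in favour of one arm, because attribution may follow perceived allocation. The article says "Participants will not be told until the end of the study which group they were allocated to", and both arms have the same blood draw, occluded syringe and enquiries. It plans to assess blinding, and it gives no attribution rates by arm. Any spurious risk ratio would have to come from invented figures.
- **The schedule is consistent.** The text and Table 1 agree on 2 and 12 months, the early enquiries cover the period closest to exposure, and health service use is collected at 2, 6, 9 and 12 months for the economic evaluation. The timing is therefore a design choice and not an error. However, the article does not say that the service-use data feed adverse event reporting, and they may miss self-bought analgesics.

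None of these replies answers the wording of the serious definition. It is a stated rule, not a detail left to another document.

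**Conclusion.** The point holds in two limited parts. First, the serious adverse event definition includes a condition that has nothing to do with seriousness. Followed literally, it moves expected serious events into the non-serious count. This rests only on the two definitions in the same paragraph. Second, the only content described for the 2- and 12-month self-report depends on the participant's view of cause, which fits poorly with a definition that disregards cause. Events that participants do not attribute to treatment may be under-recorded after the injection visits. This part assumes that the forms follow the article's description.

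Neither effect can be sized from the document. Differential undercounting between arms is not established, and no primary or secondary efficacy result is affected. The case for changing the text is that the serious event count should mean what readers will take it to mean, and the correction is very cheap.

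**What to change.** 1. Delete the words *and unexpected* from the serious adverse event definition, and record expectedness as a separate field for each event.
2. Have the 2- and 12-month questions ask about all adverse events, with perceived relatedness to the study treatment as a follow-up item. If the forms already do this, a clarifying sentence is enough.
3. Optionally, add the adverse event and co-intervention items to the questionnaires already sent at 6 and 9 months. The longest interval between enquiries would fall from 10 months to 6 − 2 = 4 months.

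The first two changes need a short protocol amendment, one extra data field and a revised form. The third adds slightly to participant burden. None needs a new visit or a new role.

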Participants will be excluded if they:i.have Kellgren and Lawrence grade 1 (indicating questionable disease) or grade 4 (indicating severe disease);ii.have lateral joint space narrowing greater than or equal to medial joint space narrowing on x-ray using the Osteoarthritis Research Society International (OARSI) atlas [21];iii.had injection into the target knee joint of glucocorticoid in the past 3 months or hyaluronic acid in the past 6 months,iv.had any autologous blood product or stem cell preparation in the past;v.had knee surgery on their target knee within past 12 months;vi.have systemic or inflammatory joint disease such as rheumatoid arthritis;vii.have a history of crystalline or neuropathic arthropathy;viii.had a knee joint replacement or high tibial osteotomy on their target knee;ix.plan for joint surgery in the target knee in next 12 months;x.have other muscular, joint or neurological condition affecting lower limb function;xi.have a needle phobia;xii.have immunosuppression or acute infective processes;xiii.have cancer or other tumours in the last 3 years, or undergone any treatment for cancer or tumours in the last 3 years;xiv.have a bleeding disorder or are receiving anti-coagulation therapy;xv.have the presence of a warm, tense joint effusion;xvi.have a platelet count < 150,000/μL;xvii.have any other medical condition precluding participation in the study including contraindication to MRI such as a pacemaker;xviii.pregnancy;xix.are unwilling to discontinue non-steroidal anti-inflammatory drug and other analgesic usage, with the exception of paracetamol for rescue pain relief, from 2 weeks before the baseline assessment until the 12-month follow-up assessment;xx.have a body mass index (BMI) > 40 kg/m^2^ because of problems fitting into the MRI machine knee coil;xxi.unable to attend the six study appointments over 12 months; andxxii.cannot understand written/spoken English.

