#### Economic analyses

The cost-effectiveness of PRP will be estimated by calculating the incremental average health care cost of those treated and the difference in pain score and health-related quality of life over the 12 months of the trial compared to the placebo group. The comparison will be reported as the incremental cost per unit change in the pain score, the incremental cost per additional quality-adjusted life year, and the net benefit of treatment at 12 months. The quality-adjusted life year will be calculated using the average AQoL-8D value. Net benefits will be calculated using a range of potential money values of a quality-adjusted life year. Costs will include the cost of treatment and associated imaging as well as the downstream medical, pharmaceutical and hospital costs in each arm. Health care utilisation data will be collected by questionnaire. Cost-effectiveness will be calculated using separate generalised linear regression models for costs and outcomes controlling for baseline levels. Predicted costs and outcomes will be used to calculate means for cost-effectiveness ratios and net benefits with bootstrapped 95% confidence intervals. If there is no demonstrated benefit from PRP, we will calculate the incremental average health care cost of those treated. In the secondary economic analysis, the impact on employment and productivity at work will be calculated from data collected by questionnaire.

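### Co-interventions and drug use, and adverse events after the injection visits, are scheduled for collection only at 2 and 12 months, although questionnaires already go out at 6 and 9 months

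*Protocol article*

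**What the plan says.** The section on adverse effects and co-interventions sets the collection times. For other treatments: "Use of co-interventions (medications for knee pain and any other treatments for knee OA) will be recorded at 2 and 12-months". For harms: "Adverse events will be collected via self-report during the 2- and 12-month data collection, and by the study nurse following each injection". The Interventions section describes the nurse's part: "After each injection, the study nurse will ask the participant if they experienced any adverse events following the previous injection".

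Table 1 agrees with the text. It marks adverse events and co-interventions at 2 and 12 months, and drug or supplement use at baseline, 2 and 12 months.

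Contact with participants is more frequent than that. Under Procedures: "Paper-based or electronic clinical and health outcome questionnaires will be sent to participants at 2, 6, 9 and 12 months". Overall knee pain, AQoL-8D and the health economic data are all scheduled at 6 and 9 months.

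The analgesic restriction covers the whole period. Candidates are excluded if they "are unwilling to discontinue non-steroidal anti-inflammatory drug and other analgesic usage" from 2 weeks before baseline to the 12-month assessment, with paracetamol allowed as rescue. Procedures repeats the request.

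**The concern.** Participants enter with pain of at least 4 out of 10 and are asked to keep to the restriction for a year, so some departures are foreseeable. For most of that year no drug-use or co-intervention item is scheduled that would show them, and pain is scored at 6 and 9 months without such an item alongside.

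Two descriptive results depend on this record. The first is how much other treatment each arm used, and when. A reader will want it to interpret both primary outcomes, since cartilage change builds up over the full 12 months and the Background itself cites a possible small harmful effect of repeated corticosteroid injections on cartilage. The second is the later safety record. After month 2 it rests on one self-report at month 12, which asks for the nature and duration of each event and the action taken. Such detail is harder to recover the longer the interval.

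**Working it through.** **Inputs** (Table 1; Adverse effects of treatment and co-interventions; Interventions; Procedures)

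| Item | Times after the first injection |
|---|---|
| Nurse enquiry about adverse events | weeks 0, 1 and 2 |
| Self-reported adverse events | 2 and 12 months |
| Co-interventions; drug/supplement use | 2 and 12 months (drug use also at baseline) |
| Overall knee pain | 2, 6, 9 and 12 months |
| Health service use (economic data) | 2, 6, 9 and 12 months (also baseline) |
| Questionnaires sent | 2, 6, 9 and 12 months |

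**Intervals as planned.** Collection points 0, 2 and 12 months give 2 − 0 = 2 and 12 − 2 = 10 months. The longer interval is 10/12 = 83% of follow-up.

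**Effect of the nurse's enquiries.** The last falls at week 2, and the 2-month questionnaire covers the time from there to month 2. The early period is therefore well covered for adverse events, but nothing is added after month 2. The 10-month interval is unchanged.

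**Intervals if the existing 6- and 9-month questionnaires carried the items.** Collection points 0, 2, 6, 9 and 12 months give 2, 4, 3 and 3 months. The longest falls from 10 to 4.

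**Does anything in the sample size depend on this?** The stated figures reproduce. With δ = 0.40 × 2.8 = 1.12 percentage points, SD 3.5 and correlation 0.50, n per arm = 2 × [3.5 × √(1 − 0.50²) × (1.960 + 0.842) / 1.12]² = 114.97, rounded up to 115. Then 115/0.80 = 143.75, rounded up to 144 per arm and 288 in total. For pain (1.8 units, SD 2.4, correlation 0.29), power at 115 per arm exceeds 99.9%, which agrees with the stated figure above 99%. Collection times for co-interventions and adverse events enter none of these formulas.

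**The case against.** The strongest reply is that the gap is partly filled. The health economic data are "measured using data collected at baseline, and 2, 6, 9 and 12-months. Data include health care costs estimated from healthcare service usage", and the Economic analyses section adds: "Health care utilisation data will be collected by questionnaire". It also says: "Costs will include the cost of treatment and associated imaging as well as the downstream medical, pharmaceutical and hospital costs in each arm". An injection from another doctor, or an adverse event that led to a consultation or admission, is health service use and may well be picked up at 6 or 9 months. This stands as a partial offset. It would be wrong to say that the 6- and 9-month pain scores have no treatment record at all. But the article does not say that these items cover over-the-counter analgesics, identify treatment of the study knee, or capture events for which no care was sought.

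Secondly, the main comparisons match the recording times. The primary endpoint is at 12 months, pain refers to the last week, and changes are presented at 2 and 12 months. Current medication at those times needs no long recall. This also stands, and it limits the point to the description of the period between.

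Thirdly, the article gives no recall window for the 12-month items, and diaries or between-visit event reporting may be set out in the full protocol, which is not shown. A 10-month recall is thus an inference from the schedule. If the window is 10 months, recall is long; if it is short, part of the interval is not asked about by these items at all.

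A reader might infer two stronger things. One is that the planned full-adherence analysis is undermined. The documents do not support this: adherence there is to assigned treatment, and Participant compliance is reported as the number of injections given, so that analysis as written needs no co-intervention data. The other is that unrecorded treatment dilutes the pain difference by a calculable amount. The article gives no rates of use by arm and no effect of such use. Any dilution would come from the use itself, and better recording would not remove it from the intention-to-treat contrast.

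**Conclusion.** The point holds as a limited design weakness. Text and Table 1 agree, so nothing is contradictory or miscalculated. The stated schedule leaves 10 of 12 months without a dedicated item on drug use, co-interventions or adverse events, although two questionnaires are sent in that time. The loss is in the completeness and timing of the later safety record and in the description of other treatment by arm. Its size cannot be put in numbers beyond the interval itself, because the article gives no figure for recall error or rates of use. The conclusion assumes that the full protocol has no further routine collection between months 2 and 12, and that the health service items do not already cover non-prescription drugs, knee-specific treatment and untreated events. If they do, the point shrinks accordingly. The sample size and the primary intention-to-treat estimate are unaffected.

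**What to change.** Add the medication, co-intervention and adverse-event items already used at 2 and 12 months to the 6- and 9-month questionnaires, with each item asking about the time since the previous questionnaire. Change Table 1 and the section on adverse effects and co-interventions to match. State there what the health service use items cover, so that the two sources can be read together.

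The cost is a minor amendment and a few more items in two existing questionnaires, with no new visits and slight extra burden. Recruitment began in August 2017 and was expected to run to December 2019, so earlier participants would keep the 10-month interval and later ones would have intervals of 3 to 4 months. Record which version each participant received and report the counts with that in view. Allocation is 1:1 in small blocks within strata, so the change should fall about equally on the two arms, but pooled event rates would mix two recall windows.
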